# Refers to Non-injection-site pain other than muscle pain, Arthralgia and headache

### General principles for the grading for other adverse events

The intensity of adverse events not mentioned in the rating table shall be evaluated according to the following criteria:

| Grade 1                                                                    | Grade 2                                                    | Grade 3                                             | Grade 4                                                | Grade 5 |
|----------------------------------------------------------------------------|------------------------------------------------------------|-----------------------------------------------------|--------------------------------------------------------|---------|
| Mild: Short-term
(< 48 hours) or
mild discomfort,
no influence on | Moderate: Mild
or moderate
restricted
activities, | Severe:
Significant
restricted
activities, | Critical:
Life-threatening
possibly,
severely | Death   |

| Grade 1                                   | Grade 2                                                                                                | Grade 3                                                                                 | Grade 4                                                  | Grade 5 |
|-------------------------------------------|--------------------------------------------------------------------------------------------------------|-----------------------------------------------------------------------------------------|----------------------------------------------------------|---------|
| activities,
treatment not
indicated | presentation
indicated
possibly,
treatment not
indicated or
mild treatment
indicated | presentation and
treatment
indicated,
hospitalization
indicated
possibly | restricted
activities,
intensive care
indicated |         |

### 5.5.3 Outcome of AEs

The outcomes of ARs/AEs include: (1) Recovery; (2) Not yet recovered; (3) Recovered but sequelae; (4) Death; (5) Loss of visit.

### 5.5.4 Relationship between AE and vaccination

5=Definitely related: There is evidence of administration of the investigational vaccine; the adverse event occurs in a plausible time relationship to administration of the investigational vaccine; the occurrence of the adverse events is explained by the investigational vaccine more reasonably than other reasons; a positive result is observed after re-administration of the investigational vaccine; the adverse events are consistent with previous knowledge of this or this type of vaccine.

4=Probably related: There is evidence of administration of the investigational vaccine; the adverse event occurs in a plausible time relationship to administration of the investigational vaccine; the occurrence of the adverse event is explained by the investigational vaccine more reasonably than other reasons.

3=Possibly related: There is evidence of administration of the investigational vaccine; the adverse event occurs in a plausible time relationship to administration of the investigational vaccine; administration of the investigational vaccine cannot be ruled out as a cause of the adverse event, but other reasons may be the cause.

2=Unlikely related: There is evidence of administration of the investigational vaccine; the adverse event is more likely to be caused by other reasons; a negative or uncertain result is observed after re-administration of the investigational vaccine.

1=Definitively unrelated: The subject has not used the investigational vaccine; or the adverse event occurs in an implausible time relationship to administration of the investigational vaccine; or there are other significant reasons that may result in the adverse event.

### **5.5.5 Treatment of AEs/ARs**

An adverse event (AE) is any untoward medical occurrence in a patient or clinical trial participant administered with a pharmaceutical product and which does not necessarily have a causal relationship with this treatment.

Adverse reactions (AR): unexpected or harmful reactions in the process of vaccination according to the prescribed dose and procedure, usually related to vaccination.

Serious adverse event (SAE): refers to the following important medical events, whether or not related to the vaccine clinical trial, including: 1) death; 2) life threatening; 3) hospitalization or prolonged hospitalization; 4) permanent or significant disability / loss of function; 5) congenital abnormality or birth defect; 6) severe adverse event It may lead to other important medical events, such as those listed above without treatment.

Suspected Unexpected Serious Adverse Reaction (SUSAR): Suspected adverse reactions refer to the adverse reactions of subjects at any dose that have nothing to do with the purpose of the medication. After analysis, it is considered that the relationship with the drug is at least likely to be related; Unexpected refers to adverse reactions. The nature, extent, consequences, or frequency are different from the expected risks described in the previous plan or other related materials (such as the investigator's manual and instructions).

If subject have any clinically significant disease/event after vaccination, it should be reported to the investigator as soon as possible. The investigator should follow up the adverse reaction/event until the symptoms disappear or the symptoms stabilize. When the investigator deems it necessary, the necessary treatment and treatment will be provided unconditionally to relieve the pain caused by the adverse reaction/event for the subject. All drug treatment and medical treatment will be recorded at each

follow-up.

In the event of a serious adverse event/reaction, the investigator should take necessary measures quickly, fill in the "Serious Adverse Event Report Form" within 24 hours, and report it to the main investigator in the form of fax or E-mail.

#### **5.5.6 Reporting procedures for SAE**

Any SAE, whether related to injection vaccine or not, must be reported to the principal investigator via fax or E-mail within 24 hours of being informed of the SAE Report Form: This includes descriptions of AE, timing and type of onset, duration, intensity, causality with vaccination, outcomes, management (symptomatic treatment), and other relevant clinical and laboratory data.

Upon receiving the report of a SAE, the principal investigator, together with the safety observer, decided whether the subjects should continue to participate in the study or terminate the study early, taking into account the duration, extent, intensity, outcome and willingness of the subjects. The principal investigator should determine whether the SAE is suspected and not SUSAR. If so, the principal investigator should report to the vaccine manufacturer, the Drug Evaluation Center of the General Administration and the National Health Commission in time.

For suspicious and SUSAR that are fatal or life-threatening, the principal investigator should report to the Drug Evaluation Center of the General Administration as soon as possible after first being informed, but within 7 natural days, and within the following 8 days to improve the follow-up information.

Note: The first day principal investigator be aware of the event is Day 0.

For suspicious and SUSAR of non-fatal or life-threatening, or other potentially SAE, the principal investigator should report to the Drug Evaluation Center of the General Administration as soon as possible after first received the information, but within 15 natural days. SAE should be truthfully recorded, evaluated and discussed in the boost report after completion or termination of the trial.

#### **5.5.7 Clinical assessment**

The investigator should report any AE with clinical manifestations as soon as he/she becomes aware of the subject after vaccination, and conduct timely

investigation and medical visit, such as medical record, physical examination and necessary laboratory examination, as well as appropriate medical treatment. For SAR/SAE, follow-up should continue until the serious adverse events are resolved and a detailed investigation and follow-up record should be completed, including the following:

- 1) Description of AE;
- 2) Start and end time of AE;
- 3) Strength grading;
- 4) association with vaccination;
- 5) Laboratory test results;
- 6) Treatment measures.

#### **5.5.8 Treatment of pregnancy events**

Vaccination of the trial is not allowed during pregnancy. Before vaccination, the subjects will be given urine pregnancy test, and those who are positive in the urine pregnancy test should not be included in the group. If pregnancy event occurred within 6 months of the visit, fill in the questionnaire of pregnancy cases.

#### **5.5.9 Combined medication/vaccine**

When the medical events happen during the study period, the participant are allowed to carry out the appropriate medical treatment, but the medical treatment should be recorded in time.

Other vaccination is not recommended except for emergency during the research period, such as rabies vaccine, tetanus vaccine, or other emergent vaccination need. Any vaccine used is required to be recorded during the study period.

### **5.6 Collection, Preservation and Transportation of samples**

#### **5.6.1 Samples collection**

V1-V4 each visit, 20ml of venous blood will be collected by vacuum anticoagulant sampling, PBMC and serum will be isolated, and the antibody level, immune cell population differentiation and antibody lineage induced by vaccine will be detected.

Blood samples from this clinical trial will be used to test the immune response indicators specified in the protocol, and the use of other studies will require the approval of the ethics committee.

### **5.6.2 Preservation and transportation of samples**

Unified operation standards are adopted in the process of preservation and transportation. The storage temperature of serum should be - 20°C and below, and it should be transported to the testing laboratory in time. The separation, transportation and preservation of BPMC used for the differentiation of immune cell population and the detection of antibody spectrum are operated by the third party laboratory according to the standard operating procedures.

## **6 Data administration**

### **6.1 Data administration**

In this study, EDC is used to collect and manage research data, and the system kept a complete modification track to ensure the traceability of clinical trial data. According to the requirements of Technical Guidelines for Clinical Trial Data Management, complete data collection, input, cleaning, consistency check, database locking and other work. The data management process should comply with the GCP specification to ensure the authenticity, integrity and accuracy of clinical trial data.

#### **6.1.1 Design and establishment of database**

The project database (eCRF) is set up by the database designer, using the CDISC standard as much as possible.

After the database is established and tested, PI, Sub-I, CRC, PM, CRA, DM, etc. of each role authority can be officially launched and applied after training.

#### **6.1.2 Data entry**

The trained data entry personnel shall complete the online data entry in time after the visit.

The researcher needs to approve the data on eCRF to verify that the data recorded in eCRF is true. After data entry is completed, any data changes need to be explained (Comments) and automatically recorded in the system.

### **6.1.3 Verification of data records**

The quality control personnel shall check the data records entered into the EDC regularly or irregularly to ensure that all the data entered are consistent with the original documents. If there are inconsistencies, quality control personnel need to send a query to the researcher at the corresponding place in the EDC system, and the researcher needs to verify the original data and update the input content until the EDC system is complete. Before locking the warehouse, quality control personnel should carefully verify the original data of the subject and the necessary signature of the researcher.

### **6.1.4 Verification of data**

The data manager will question and manage the test data according to the Data Verification Plan (DVP).

When data is input into the EDC system, if there is any illogical data, the system will automatically check and Query. These queries need to be reviewed and answered by the researcher or authorized personnel. When the updated data makes the logical check impossible, the Query will automatically shut down. Automatically closed Query, DM can review, when the problem is not solved, DM can manually add questions, and continue to communicate with the research center until the problem is solved.

In addition to automatic verification by the system, Query can be manually added to the EDC system for questions checked by SAS programming or manually checked by the data administrator when researchers need to clarify/verify/confirm.

Before locking the database, the data administrator must ensure that all queries are cleaned up and the researcher completes the electronic signature on the EDC system. To ensure the integrity and accuracy of patient data.

### **6.1.5 Medical coding**

Medical coders do the work of medical coding. Unsolicited AEs are medically coded. AE will be coded according to the MEDDRA (version 21.1 or above) dictionary.

During the coding process, DM can query to the researcher in real time online

for any failure to encode due to improper, inaccurate or ambiguous medical terms.

A medical review of the medical code is required before database locking.

#### **6.1.6 Database locking**

Complete the list of locking database. The data manager export it to the database in the specified format and hand it over to the statistician for statistical analysis. After data locking, if there is conclusive evidence that it is necessary to unlock the database, the researcher and relevant personnel should sign the unlock document.

#### **6.1.7 Outboard data manager**

Immunogenicity data is managed as external data, and data management reviews and verifies the external data.

### **6.2 Statistical Analysis**

#### **6.2.1 Selection of analysis data sets**

Safety set (SS):

The safety evaluation should be conducted for all participants who receive vaccines after randomization. Data violating the protocol should not be eliminated.

Immunogenicity data set:

Full Analysis Set (FAS): It is defined as ideal participant population determined according to the Intervention modified intention-to-treat analysis, the group of participants will be determined by the intervention they actually receive rather than they are allocated to. All participants who meet the inclusion /exclusion criteria, and are randomized and have at least one evaluable data will be included in the FAS.

Per-Protocol Set (PPS): It is a subset of FAS. Participants in this set are more compliant with the protocol, experience no major protocol violation, comply with all inclusion criteria / exclusion criteria, and complete the vaccination within the time window as required in the protocol and all blood samplings are included in the PPS set. Participants who violate the trial protocol, such as poor compliance or lost to follow-up, and those who suffer intercurrent SARS-CoV-2 infection will not be included in this analysis set.

In this trial, the FAS will be used as the primary analysis set. However, PPS should be analyzed simultaneously. Any inconsistency between PPS and FAS analysis results should be discussed in the report.

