##### **4.5.2 Complete of immunogenicity data collection**

Blood samples are collected at day 0, day 14, 28 and 6 months after immunization according to the protocol.

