### 3.2.3 Unblinding

We masked investigators, laboratory staff, and outcome assessors to the allocation of treatment groups, but not to the three-dose or two-dose regimen. In the event of a medical emergency, the principal investigator should be contacted as far as possible before disrupting the study vaccine/placebo blinding to discuss the need for an urgent unblinding.

Blinding will be uncovered when completing the initial analysis of safety and immunogenicity 28 days after the second dose, but the subjects and safety observers will remain blinded.

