## 4. Clinical Trial Endpoint

### 4.1 Primary Endpoint

- (1) The incidence of adverse reactions in each group within 28 days after the booster vaccination;
- (2) Neutralising antibodies to live SARS-CoV-2 (GMT) at 14 days after the booster vaccination.

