## **5. Statistical Analysis**

### **5.1 Selection of analysis data sets**

**Safety Set (SS):** The safety evaluation should be conducted for all participants who receive vaccines after randomization. Data violating the protocol should not be eliminated.

**Intention-to-treat analysis (ITT):** It is defined as ideal participant population determined according to the intervention modified intention-to-treat analysis, the group of participants will be determined by the intervention they actually receive rather than they are allocated to. All participants who meet the inclusion /exclusion criteria, and are randomized and have at least one evaluable data will be included.

**Per-Protocol Set (PPS):** It is a subset of ITT. Participants in this set are more compliant with the protocol, experience no major protocol violation, comply with all inclusion criteria/ exclusion criteria, and complete the vaccination within the time window as required in the protocol and all blood samplings are included in the PPS set. Participants who violate the trial protocol, such as poor compliance or lost to follow-up, and those who suffer intercurrent SARS-CoV-2 infection will not be included in this analysis set.

In this trial, the intervention modified intention-to-treat will be used as the primary analysis set. However, PPS should be analyzed simultaneously. Any inconsistency between PPS and ITT analysis results should be discussed in the report.

The above analysis sets will be discussed and decided by the principal investigator, and the statistician before the database is locked.

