## **6.10 Initial analysis**

An initial analysis of safety and immunogenicity will be performed after completing all the data collection within 28 days after the boost vaccination.

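### A single per-protocol set with no time limits lets Month 6 events remove valid Day 14 and Day 28 titres, and its final membership is not known until after the Day 28 unblinding

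*Combined protocol and SAP*

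**What the plan says.** Protocol 6.2.1 and SAP 5.1 define the PPS in nearly the same words, as a subset of the full analysis set (FAS; the SAP calls it ITT). PPS members "complete the vaccination within the time window as required in the protocol and all blood samplings are included in the PPS set". The first exclusion named is "Participants who violate the trial protocol, such as poor compliance or lost to follow-up". Infection has a clause of its own: "those who suffer intercurrent SARS-CoV-2 infection will not be included in this analysis set". No condition carries a cut-off date or visit, and neither document has a visit-specific PPS.

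The relevant timings are:
- **Draws.** Protocol 4.5.2: "Blood samples are collected at day 0, day 14, 28 and 6 months after immunization according to the protocol". The visit tables in protocol 3.3 and SAP 3.1 show the same four draws.
- **Primary immunogenicity endpoint.** SAP 4.1: "Neutralising antibodies to live SARS-CoV-2 (GMT) at 14 days after the booster vaccination". The two formal hypotheses (protocol 3.2, SAP 3.3) are placed at Day 28. Both visits precede Month 6.
- **Initial analysis.** SAP 6.10, repeated in protocol 6.2.3: "An initial analysis of safety and immunogenicity will be performed after completing all the data collection within 28 days after the boost vaccination".
- **Unblinding.** SAP 3.2.3, repeated in protocol 3.4.3: "Blinding will be uncovered when completing the initial analysis of safety and immunogenicity 28 days after the second dose". Subjects and safety observers stay blinded.

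The FAS is the primary set. The PPS is to be analysed simultaneously and any disagreement discussed in the report. SAP 5.1 leaves the sets to the principal investigator and the statistician, to be decided before database lock.

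**The concern.** A per-protocol set should leave out people whose measurement at the visit in question was compromised. A missed Month 6 draw, a loss in month 4 or an infection in month 5 cannot have changed a titre drawn on Day 14. Removing that titre conditions an early result on something that happened later, and later attendance or infection may differ by group or be related to immune response. The Day 14 and Day 28 PPS comparisons are then no longer simply randomised participants with sound early data.

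Timing adds to this. The PPS is needed when the initial analysis is run, but one of its criteria is then still open. If a provisional PPS is used, the report may carry two Day 14 PPS results from identical Day 14 titres, and the second membership list is completed after group results are known.

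What is at stake is the value of the PPS as a check. Hypothesis 1 is a non-inferiority claim, where agreement between FAS and PPS is part of the argument. A disagreement caused by Month 6 attendance would say nothing about Day 14 or Day 28.

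**Working it through.** **1. Apply the rule to cases.** Each participant below has the correct boost in window and good Day 0, Day 14 and Day 28 samples.

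| Later event | Day 14 and Day 28 titres sound? | In the PPS on the literal text? |
|---|---|---|
| None | Yes | Yes |
| Month 6 draw missed | Yes | No (all samplings required) |
| Lost after Day 28 | Yes | No |
| Infected between Day 28 and Month 6 | Yes | No, if intercurrent covers the whole study |

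Protocol 4.6 lists incomplete blood collection as a deviation (4.6.2), not a violation (4.6.1). The PPS nevertheless excludes for it.

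**2. Apply the rule at the initial analysis.** That analysis starts once Day 28 data are complete. Participants enrolled last cannot have a Month 6 sample by then, so final membership is unknown. Blinding is lifted at that point. SAP 5.1 ties the decision on the sets to database lock, but neither document specifies a lock or freeze before the Day 28 unblinding.

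**3. Reproduce the plan's sample size.** Inputs (SAP 3.3): log10 GMT 2.2 against 1.9, so a difference of 0.3 (ratio 10^0.3 = 2.0); SD 0.6; one-sided 2.5%; 90% power; margin −0.174 on the log10 scale; 10% drop-out.
- Superiority: n = 2(1.96 + 1.2816)² × 0.6² / 0.3² = 84.1, so 85. The t-test solution is 85.03, so 86 per group, as stated.
- Non-inferiority: n = 2(1.96 + 1.2816)² × 0.6² / (0.3 + 0.174)² = 33.7, so 34. The t-test solution is 34.7, so 35 per group, as stated.
- Drop-out: 86 / 0.9 = 95.6, so 96, stated as about 100.

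**4. Cost in precision.** Assume all of the 10% drop-out falls after Day 14. The documents give no timing, so this is an upper case within their own figure. The Day 14 PPS then falls from 100 to 90 per group although every Day 14 sample was taken.
- Standard error: √(100/90) = 1.054, a rise of 5.4%.
- Superiority power (t-test): 94.0% at 100 and 91.6% at 90. The normal approximation Φ(0.5√(n/2) − 1.96) gives 94.2% and 91.8%.
- Non-inferiority power at 90: Φ((0.474/0.6)√(90/2) − 1.96) = Φ(3.34), above 99.9%.

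**5. Sensitivity.** The documents give no per-visit loss. Assume an independent loss m at each draw, from 100 per group, with power from the normal approximation.

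| m | Kept, Day 0 and Day 14 only: (1−m)² | Power | Kept, all four draws: (1−m)⁴ | Power |
|---|---|---|---|---|
| 2% | 96% | 93.4% | 92% | 92.4% |
| 5% | 90% | 91.9% | 81% | 89.1% |
| 10% | 81% | 88.9% | 66% | 81.7% |

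The four-draw rule costs 1 to 7 percentage points of PPS power over this range. These powers use the plan's Day 28 assumptions and apply to Day 14 only if the same difference and SD hold there.

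**The case against.** The strongest reply has four parts.

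- **The text never names Month 6.** The PPS sentence is badly worded. Month 6 enters by reading it with the visit schedule, and intercurrent has no stated window. At the initial analysis, all blood samplings could be taken as those due so far. This stands in part. A reader might infer that a PPS cannot be formed at all at Day 28. That follows only on the literal reading, since a provisional set could be built. But no provisional or visit-specific set is pre-specified, and a rule that needs this much interpretation should be rewritten.
- **The sets can be decided before lock.** True, but with no lock specified before the Day 28 unblinding, that discretion could be used with results known. The exposure is limited: a missed draw is objective, and poor compliance is the criterion most open to judgement. SAP 3.2.1 also says investigators stay blinded throughout, which does not sit easily with SAP 3.2.3.
- **The primary analysis is the FAS.** This stands in full. A reader might infer that the main Day 14 result loses data or is biased. It does not, because the FAS asks only for at least one evaluable result.
- **The numbers show little harm.** Also correct. At 90 per group the plan's 86 and 35 are both exceeded. It is tempting to add that low responders are infected more often and so bias the PPS in a known direction. Neither document gives evidence for this, and the direction and size of any bias are unknown.

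A reader might also infer that titres drawn after an infection should come out of the FAS. The documents do not settle this. Keeping them is a legitimate choice of estimand, and dropping them would itself select on a later event. It is a separate question from the PPS.

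**Conclusion.** The point holds as a defect in a supporting analysis. One PPS with no time limits, read with the four-draw schedule, discards sound Day 14 and Day 28 titres because of later events. Its final membership would be settled after the Day 28 unblinding, so the Day 14 PPS result could change between the two analyses.

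The primary FAS result stands. Power is a minor matter: 94.0% falls to 91.6% if the whole 10% drop-out comes after Day 14, and superiority power drops below 90% only when fewer than about 86 per group remain. The harm that matters is avoidable post-baseline selection in the set that the report must compare with the FAS. The conclusion assumes that all blood samplings means all scheduled samplings and that loss and infection count throughout follow-up, which is the plain reading. It does not depend on any assumed infection rate. The change should be made because the replacement is clearly better and nearly free.

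**What to change.** In protocol 6.2.1 and SAP 5.1, replace the single PPS with three sets: PPS-D14, PPS-D28 and PPS-M6. Each requires:
- the correct boost within the protocol's window;
- no major protocol violation;
- the Day 0 sample, and that visit's sample within its window;
- no SARS-CoV-2 infection before that visit.

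A later missed draw, loss or infection then does not affect an earlier set. State that PPS-D14 and PPS-D28 are fixed before the Day 28 unblinding, are used at the initial analysis, and are carried unchanged into the final report. Compare each set with the FAS at its own visit. The FAS definition is left as it is.

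The cost is wording in two sections and three dataset flags instead of one, with no new data. The drawback is that PPS membership differs by visit, so PPS results over time do not describe one fixed group. The tables should give the number in each set by group.
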